### 7.3.6 SCHEDULE OF EVENTS TABLE

| Procedures                                                  | Recruitment and Screening Visit | Baseline Visit 0 | Visit 1 (refill) | Follow-up (Visit 2) | Visit 3 (refill) | Follow-up (Visit 4) | Visit 5 (refill) | Final Study Visit (Visit 6) |
|-------------------------------------------------------------|---------------------------------|------------------|------------------|---------------------|------------------|---------------------|------------------|-----------------------------|
| Selection of bars and recruitment of barmaids for screening | X                               |                  |                  |                     |                  |                     |                  |                             |
| Eligibility                                                 | X                               | X                |                  |                     |                  |                     |                  |                             |
| Screening/ Baseline/ Endline questionnaire                  | X                               | X                |                  |                     |                  |                     |                  | X                           |
| Informed consent                                            | X                               | X                |                  |                     |                  |                     |                  |                             |
| Demographics                                                | X                               |                  |                  |                     |                  |                     |                  |                             |
| Medical history                                             | X                               |                  |                  |                     |                  |                     |                  |                             |
| Randomization 1 (facility- vs. workplace-based)             |                                 | X                |                  |                     |                  |                     |                  |                             |
| Syphilis testing                                            | X                               |                  |                  |                     |                  |                     |                  | X                           |
| HBsAg test                                                  | X                               |                  |                  |                     |                  |                     |                  | X                           |
| Serum creatinine test                                       | X                               |                  |                  |                     |                  |                     |                  | X                           |
| HIV test                                                    | X                               |                  | X                |                     |                  | X                   |                  | X                           |
| Schedule study visits                                       | X                               |                  |                  |                     |                  |                     |                  |                             |
| Provide 28 days of emtricitabine/tenofovir disoproxil       |                                 | X                | X                | X                   | X                | X                   | X                | X                           |
| Randomization 2 (Omni-channel PrEP Champion)                |                                 | X                |                  |                     |                  |                     |                  |                             |
| Record vital signs                                          |                                 |                  |                  | X                   |                  | X                   |                  | X                           |

| Procedures                                        | Recruitment and Screening Visit | Baseline Visit 0 | Visit 1 (refill) | Follow-up (Visit 2) | Visit 3 (refill) | Follow-up (Visit 4) | Visit 5 (refill) | Final Study Visit (Visit 6) |
|----------------------------------------------------------|----------------------------------------|-------------------------|-------------------------|----------------------------|-------------------------|----------------------------|-------------------------|------------------------------------|
| TDF in urine                                             |                                        |                         |                         | X                          |                         |                            |                         | X                                  |
| Counsel on adherence                                     |                                        | X                       | X                       | X                          | X                       | X                          | X                       |                                    |
| Record adherence                                         |                                        |                         |                         | X                          |                         | X                          |                         | X                                  |
| Final HIV prevention counseling                          |                                        |                         |                         |                            |                         |                            |                         | X                                  |
| Information of follow up support by the national program |                                        |                         |                         |                            |                         |                            |                         | X                                  |
| Adverse event evaluation                                 |                                        |                         | X                       | X                          | X                       | X                          | X                       | X                                  |

#### **7.4 Concomitant Medications, Treatments, and Procedures**

None.

#### **7.5 Prohibited Medications, Treatments, and Procedures**

None.

#### **7.6 Prophylactic Medications, Treatments, and Procedures**

Not applicable.

#### **7.7 Rescue Medications, Treatments, and Procedures**

Not applicable.

#### **7.8 Participant Access to Study Agent At Study Closure**

Since the trial is working in close collaboration with MDH who are implementors of the PrEP national program there will be no problem at the end of the study to link participants to PrEP service provided by the national PrEP program if they wish.

## 8. ASSESSMENT OF SAFETY

### 8.1 SPECIFICATION OF SAFETY PARAMETERS

#### 8.1.1 DEFINITION OF ADVERSE EVENTS (AE)

Adverse event means any untoward medical occurrence associated with the use of an intervention in humans, whether or not considered intervention-related (21 CFR 312.32 (a)).

#### 8.1.2 DEFINITION OF SERIOUS ADVERSE EVENTS (SAE)

Serious adverse event or serious suspected adverse reaction. An AE or suspected adverse reaction is considered "serious" if, in the view of either the investigator or sponsor, it results in any of the following outcomes: death, a life-threatening adverse event, inpatient hospitalization or prolongation of existing hospitalization, a persistent or significant incapacity or substantial disruption of the ability to conduct normal life functions, or a congenital anomaly/birth defect. Important medical events that may not result in death, be life-threatening, or require hospitalization may be considered serious when, based upon appropriate medical judgment, they may jeopardize the patient or subject and may require medical or surgical intervention to prevent one of the outcomes listed in this definition (21 CFR 312.32 (a)).

#### 8.1.3 DEFINITION OF UNANTICIPATED PROBLEMS (UP)

This study will use the United States Department of Health and Human Services' Office for Human Research Protection's (OHRP) definition of UP. OHRP considers unanticipated problems involving risks to participants or others to include, in general, any incident, experience, or outcome that meets **all** of the following criteria:

- Unexpected in terms of nature, severity, or frequency given (a) the research procedures that are described in the protocol-related documents, such as the IRB-approved research protocol and informed consent document; and (b) the characteristics of the participant population being studied;
- Related or possibly related to participation in the research ("possibly related" means there is a reasonable possibility that the incident, experience, or outcome may have been caused by the procedures involved in the research); and

- Suggests that the research places participants or others at a greater risk of harm (including physical, psychological, economic, or social harm) than was previously known or recognized.

## 8.2 CLASSIFICATION OF AN ADVERSE EVENT

### 8.2.1 SEVERITY OF EVENT

For AEs not included in the protocol defined grading system, the following guidelines will be used to describe severity:

- **Mild** – Events require minimal or no treatment and do not interfere with the participant's daily activities.
- **Moderate** – Events result in a low level of inconvenience or concern with the therapeutic measures. Moderate events may cause some interference with functioning.
- **Severe** – Events interrupt a participant's usual daily activity and may require systemic drug therapy or other treatment. Severe events are usually potentially life-threatening or incapacitating.

### 8.2.2 RELATIONSHIP TO STUDY AGENT

The clinician's assessment of an AE's relationship to study agent (drug) is part of the documentation process, but it is not a factor in determining what is or is not reported in the study. If there is any doubt as to whether a clinical observation is an AE, the event should be reported. All AEs must have their relationship to study agent assessed. In a clinical trial, the study product must always be suspect. To help assess, the following guidelines are used.

- **Related** – The AE is known to occur with the study agent, there is a reasonable possibility that the study agent caused the AE, or there is a temporal relationship between the study agent and event. Reasonable possibility means that there is evidence to suggest a causal relationship between the study agent and the AE.
- **Not Related** – There is not a reasonable possibility that the administration of the study agent caused the event, there is no temporal relationship between the study agent and event onset, or an alternate etiology has been established.

### **8.2.3 EXPECTEDNESS**

The Tanzanian PI will be responsible for determining whether an AE is expected or unexpected. An AE will be considered unexpected if the nature, severity, or frequency of the event is not consistent with the risk information previously described for the study agent.]

## **8.3 TIME PERIOD AND FREQUENCY FOR EVENT ASSESSMENT AND FOLLOW-UP**

The occurrence of an AE or SAE may come to the attention of study personnel during study visits and interviews of a study participant presenting for medical care, or upon review by a study monitor. All AEs including local and systemic reactions not meeting the criteria for SAEs will be captured on the appropriate RF. Information to be collected includes event description, time of onset, clinician's assessment of severity, relationship to study product (assessed only by those with the training and authority to make a diagnosis), and time of resolution/stabilization of the event. All AEs occurring while on study must be documented appropriately regardless of relationship. All AEs will be followed to adequate resolution.

Any medical condition that is present at the time that the participant is screened will be considered as baseline and not reported as an AE. However, if the study participant's condition deteriorates at any time during the study, it will be recorded as an AE. UPs will be recorded in the data collection system throughout the study.

Changes in the severity of an AE will be documented to allow an assessment of the duration of the event at each level of severity to be performed. AEs characterized as intermittent require documentation of onset and duration of each episode.

The PI will record all reportable events with start dates occurring any time after informed consent is obtained until 7 (for non-serious AEs) or 30 days (for SAEs) after the last day of study participation. At each study visit, the investigator will inquire about the occurrence of AE/SAEs since the last visit. Events will be followed for outcome information until resolution or stabilization.

## **8.4 REPORTING PROCEDURES**

### **8.4.1 ADVERSE EVENT REPORTING**

Any study staff member being made aware of an AE will complete a AE Form and submit to a study PI within 72 hours of site awareness. The study PI will report this AE to the Tanzanian National Institute for Medical Research (NIMR) IRB within 3 business days to the Heidelberg IRB within 5 business days. All AEs will be followed until satisfactory resolution or until the site investigator deems the event to be chronic or the adherence to be stable. Other supporting documentation of the event may be requested by the PIs or the DSMB and should be provided as soon as possible.

#### **8.4.2 SERIOUS ADVERSE EVENT REPORTING**

The study clinician will complete a SAE Form within the following timelines:

- All deaths and immediately life-threatening events, whether related or unrelated, will be recorded on the SAE Form and submitted to a study PI within 24 hours of site awareness.
- Other SAEs regardless of relationship to the study will be submitted to a study PI within 72 hours of site awareness.

All SAEs will be followed until satisfactory resolution or until the site investigator deems the event to be chronic or the adherence to be stable. Other supporting documentation of the event may be requested by the PIs or the DSMB and should be provided as soon as possible. The study PIs will be responsible for notifying the FDA and NIMR of any unexpected fatal or life-threatening suspected adverse reaction as soon as possible but in no case later than 7 calendar days after the PI's initial receipt of the information.

#### **8.4.3 UNANTICIPATED PROBLEM REPORTING**

Incidents or events that meet the OHRP criteria for UPs require the creation and completion of an UP report form. It is the site investigator's responsibility to report UPs to their IRB and to the study PI. The UP report will include the following information:

- Protocol identifying information: protocol title and number, PI's name, and the IRB project number;
- A detailed description of the event, incident, experience, or outcome;
- An explanation of the basis for determining that the event, incident, experience, or outcome represents an UP;

- A description of any changes to the protocol or other corrective actions that have been taken or are proposed in response to the UP.

To satisfy the requirement for prompt reporting, UPs will be reported using the following timeline:

- UPs that are SAEs will be reported to the study PIs within 24 hours of the site becoming aware of the event, to NIMR IRB within 3 business days and to the Heidelberg IRB within 5 business days.
- Any other UP will be reported to the study PIs within 48 hours of the site becoming aware of the event, to NIMR IRB within 3 business days and to the Heidelberg IRB within 5 business days.

#### **8.4.4 EVENTS OF SPECIAL INTEREST**

None.

#### **8.5 STUDY HALTING RULES**

The study will be halted for a safety review if four (4) SAEs are reported, or two (2) SAEs judged by the Steering Committee to be likely related to study procedures.

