#### **8.6 SAFETY OVERSIGHT**

Safety oversight will be under the direction of a DSMB composed of individuals with the appropriate expertise, including a Tanzanian clinician, clinicians with experience working on antiretroviral treatment or prevention projects and a biostatistician. The DSMB will meet every three months to assess safety and efficacy data on each arm of the study. The DSMB will operate under the rules of an approved charter that will be written and reviewed at the organizational meeting of the DSMB. At this time, each data element that the DSMB needs to assess will be clearly defined.

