## 9.4 Measures to Minimize Bias

### 9.4.1 ENROLLMENT/ RANDOMIZATION/ MASKING PROCEDURES

The study will involve a cluster two sequential, independent randomized study. First, bars will be randomized at screening into either workplace-based or facility-based PrEP initiation and follow-up. Second, individuals will be concurrently randomized into either PrEP Champion intervention or no- PrEP Champion intervention for adherence and follow-up support. Anticipating that PrEP initiation will be approximately 10% in the facility-based arm vs. 25% in the workplace-based arm based on previously published studies in the region, we will randomize to either the facility-based arm or the workplace-based arm in a 2:5 ratio in order to obtain balance for ascertaining the second, more expensive outcome, 6-month adherence. If, as hypothesized, PrEP initiation is higher in the community- than the facility-based groups, our first primary outcome is powered to account for this unbalanced design. Under our primary hypothesized difference, in which 10% of those offered facility-based PrEP and 25% of those offered workplace-based PrEP join our study, the four study groups for our second primary outcome and secondary outcomes will look as in the table below:

|                                                               | Workplace-based
PrEP provision | Facility-based
PrEP provision |
|---------------------------------------------------------------|-----------------------------------|----------------------------------|
| Omni-channel PrEP Champion intervention
for PrEP adherence | 40                                | 40                               |
| National standard of care for PrEP adherence                  | 40                                | 40                               |

Individuals who discontinue the study early will not be replaced; since the primary endpoint is measured as urine level of TDF, they will automatically be assigned the value of zero. This non-replacement will not affect power, since by assigning discontinuing individuals a final outcome value no loss of sample size results.

The study will necessarily not be blinded. From the participants' side they will know which of the four study groups they are in based on the intervention they receive; from the investigators' side they will know who is receiving and not receiving workplace-based PrEP delivery and is part of an Omni-channel PrEP Champion intervention group.

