## 13. STUDY ADMINISTRATION

### 13.1 STUDY LEADERSHIP

The Steering Committee will govern the conduct of the study. The Steering Committee will be composed of the study PIs and independent subject matter experts.

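### The two-SAE halting trigger in section 8.5 turns on a relatedness judgement by a Steering Committee that includes the study PIs, and the DSMB that directs safety oversight has no stated part in it

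*Protocol*

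**What the plan says.** Section 8.5 of the protocol contains two triggers. The first is a count: "The study will be halted for a safety review if four (4) SAEs are reported". The second needs a judgement: "or two (2) SAEs judged by the Steering Committee to be likely related to study procedures". The section does not say who carries out the safety review, and it does not mention the DSMB.

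Section 13.1 describes the body that makes the judgement: "The Steering Committee will govern the conduct of the study". On membership it says: "The Steering Committee will be composed of the study PIs and independent subject matter experts". It gives no proportion of independent members, no voting rule and no recusal rule for the PIs.

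Section 8.6 gives oversight of safety to another body: "Safety oversight will be under the direction of a DSMB composed of individuals with the appropriate expertise". Its one fixed contact with the data is periodic: "The DSMB will meet every three months to assess safety and efficacy data on each arm of the study". Its operating rules are left to a charter that was still to be written.

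Section 8.4 names the PIs, the NIMR and Heidelberg IRBs and the FDA as recipients of event reports. Sections 8.4.1 and 8.4.2 allow the DSMB to ask for supporting documents. Section 5.5 lists the sponsor, the IRB and/or the FDA as those to be satisfied before a suspended study resumes.

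**The concern.** The two-SAE trigger exists to prompt a review earlier than the plain count would when the events look related to the study. Whether it does so depends on a relatedness judgement. The protocol gives that judgement to the committee that runs the study, with the PIs among its members, and not to the independent board that it sets up to direct safety. A board of that kind normally exists so that people with an interest in the study continuing do not decide whether a safety threshold has been met.

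At stake is the timing of a safety review. If the committee does not find two events related, the study carries on until the fourth SAE is reported. No endpoint, analysis or sample size figure is affected.

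**Working it through.** No calculation tests this point. The protocol gives no expected SAE rate and no operating characteristics for the halting rule, so there is no figure to reproduce. The check has two parts: where the judgement can change the outcome, and what role each body has.

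**Where the judgement matters (section 8.5)**

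| SAEs reported | Does a halt follow? | Does the committee's judgement matter? |
|---|---|---|
| 0 or 1 | No; neither trigger can be met | No |
| 2 | Only if both are judged likely related | Yes |
| 3 | Only if at least two are judged likely related | Yes |
| 4 or more | Yes, on the count alone | No |

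The judgement is decisive at two or three reported SAEs and nowhere else. If relatedness is not found, the threshold in effect moves from 2 to 4, which is 4 − 2 = 2 further SAEs before a review is compulsory.

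**Who has which role**

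| Step | Body named | DSMB named? |
|---|---|---|
| First receipt of SAE reports (8.4.2) | Study PIs, within 24 or 72 hours | No |
| Onward reports with a timeline (8.4.1 to 8.4.3) | NIMR IRB, Heidelberg IRB, FDA | No |
| Request for supporting documents (8.4.1, 8.4.2) | PIs or DSMB | Yes, as an option |
| Relatedness judgement for the two-SAE trigger (8.5) | Steering Committee | No |
| Safety review after a halt (8.5) | Nobody named | No |
| Resumption (5.5) | Sponsor, IRB and/or FDA | No |
| General safety oversight (8.6) | DSMB, meeting every three months | Yes |

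The DSMB has the general mandate and an optional right to ask for documents, but no assigned part in triggering, reviewing or lifting a halt. The right to ask presupposes that it knows of an event, and no timeline tells it of one. If the charter adds nothing, it could first learn of an SAE at its next quarterly meeting. That could be up to three months later, which is 3/6 = half of a woman's six months in the study.

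**The case against.** The best defence is that the sections can be read together: the committee can set off a review, and the DSMB directs safety once it is set off. That stands as far as it goes. A reader might infer that sections 8.5 and 8.6 contradict each other on who directs safety. The text does not support this, because 8.5 allocates one input to one trigger and is silent on the review. The two sections are misaligned.

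Several safeguards also stand:

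- The four-SAE trigger needs no relatedness judgement and acts as a backstop.
- Independent experts sit on the committee, so the judgement is not the PIs' alone. Nothing, however, gives the experts a majority or keeps the PIs from voting.
- IRBs receive reports promptly. Section 8.4.1 sends AEs to the NIMR IRB within 3 business days and the Heidelberg IRB within 5, and section 8.4.3 sets the same times for unanticipated problems that are SAEs. Neither IRB is given the section 8.5 judgement.
- Section 14 requires actual and perceived conflicts of interest to be managed. It is a general policy and does not address this vote.
- The charter, which is not shown, could add ad hoc contact with the DSMB. It could not move a judgement that section 8.5 assigns by name to another body.

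Three further inferences should not be drawn. First, relatedness is not the only judgement in the rule: under section 8.1.2, seriousness rests on the view of the investigator or sponsor, and it feeds both triggers. Second, although section 9.4.1 says "The study will necessarily not be blinded", the point does not rest on that. Both delivery groups receive the same drug, the triggers count SAEs over the whole study, and the documents do not show how knowing the group would sway a relatedness call. Third, no probability of a missed halt can be given. Any assumed chance of recognising a related event would apply equally to a DSMB and so would not measure what the change gains.

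**Conclusion.** The point holds in a limited form. As written, section 8.5 lets members of the body that governs the study, including its PIs, vote on whether the lower of two safety triggers fires. The DSMB that section 8.6 puts in charge of safety oversight has no stated role in that trigger, the subsequent review or resumption, and no stated route by which SAEs reach it.

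The exposure is confined to the period when two or three SAEs have been reported, and it amounts to at most two further SAEs before the count forces a review. How often the study would be in that period cannot be said, because the protocol gives no SAE rate. The conclusion rests on the protocol text alone and assumes that the unseen charter does not try to reassign the judgement; if it did, it would conflict with section 8.5. This is a worthwhile, inexpensive improvement in governance. It is not evidence that the trial is unsafe or that its results would be biased.

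**What to change.** In section 8.5, assign to the DSMB both the relatedness judgement for the two-SAE trigger and the safety review that follows either trigger, with the DSMB contacted ad hoc between its quarterly meetings. State that the PIs supply the case report but do not vote. Add the DSMB to the SAE reporting route in section 8.4 so that ad hoc contact can work. Reconcile sections 8.5, 8.6, 5.5 and 13.1 on who judges, who reviews and what part the DSMB has in resumption. Leave the trigger counts as they are.

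The cost is about one sentence in section 8.5, matching wording in the other sections and a line in the DSMB charter. The downside is an occasional message or call to DSMB members when an SAE occurs. No new body or staff is needed.
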